## Abstract

**Background:**

Asthma is the most common chronic condition in children. For many, the disease is inadequately controlled, which can burden the lives of children and their families as well as the health care system. Improved use of the best available scientific evidence by primary care practitioners could reduce the need for hospital care and improve quality of life and asthma control, thereby reducing overall costs to society and families.

**Objective:**

The Primary Care Pathway for Childhood Asthma aims to improve the management of children with asthma by (1) providing primary care practitioners with an electronic guide (a clinical pathway) incorporated into the patient’s electronic medical record, and (2) providing train-the-trainer education to chronic disease management health professionals to promote the provision of asthma education in primary care.

**Methods:**

The research will utilize a pragmatic cluster-controlled design, quantitative and qualitative research methodologies, and economic evaluation to assess the implementation of a pathway and education intervention in primary care. The intervention will be analyzed for effectiveness, and if the results are positive, a strategy will be developed to implement delivery to all primary care practices in Alberta.

**Results:**

The research has been successfully funded and ethics approvals have been obtained. Practice recruitment began fall 2015, and we expect all study-related activities to be concluded by March 2018.

**Conclusions:**

The proposed pathway and education intervention has the potential to improve pediatric asthma management in Alberta. The intervention is anticipated to result in better quality of care for equal or lesser cost.

**ClinicalTrial:**

ClinicalTrials.gov NCT02481037; https://clinicaltrials.gov/ct2/show/NCT02481037 (Archived by WebCite at http://www.webcitation.org/6fPIQ02Ma).

## Introduction

### Background and Overview

Asthma is the most common chronic disease of childhood [1-5]. At least 15% of Canadian children are affected by this disease, and over 50% of these cases are poorly controlled [3-6]. Asthma is among the top 10 reasons for Albertan children to visit an emergency department and the top 5 reasons for urgent admissions to hospital [7,8]. As compared with healthy children, children with asthma miss three times as many school days [9,10] and have substantially reduced quality of life [11,12]. From a societal perspective, inadequate asthma control also presents a considerable economic burden due to the costs associated with hospital and emergency department admissions, medications, and caregiver productivity losses [13].

High-quality evidence exists regarding how to best manage childhood asthma in a primary care setting to optimize control and minimize acute disease exacerbations [14-16]. The best treatment varies depending on the child’s asthma disease phenotype, of which there are broadly two types. Although the terms used vary, we refer to these types as “persistent/seasonal disease” and “intermittent/viral triggered” [16-18]. Persistent/seasonal disease has continuous symptoms and is often triggered by allergens, exercise, cold air, and viral illnesses, whereas intermittent/viral-triggered disease is predominately provoked by viral upper respiratory tract infections and resolves completely between infections. For most children with persistent/seasonal disease, inhaled corticosteroids substantially reduce ongoing symptoms, bronchodilator use, asthma exacerbations, and health care utilization [14-17]. For children with intermittent/viral-triggered disease, montelukast (Singulair) has been shown to substantially reduce wheezing exacerbations, asthma symptoms, and health care utilization [19-21].

Although some studies have demonstrated methods to optimize asthma outcomes and minimize costs, this does not guarantee that patients actually receive the best care. It is estimated that across the spectrum of health care, 30-40% of patients do not receive treatments of proven effectiveness [22,23]. Studies from the United States have shown that primary care practitioners do not use preventive medications in up to 45% of children with asthma [24,25], and unpublished data (2008-2011) reported by *Alberta Health Services (AHS)* from Alberta pharmacies show that about 50% of children with asthma who are treated with rescue beta-agonists do not also receive preventative medications [26].

Clinical pathways are a common strategy for changing professional behavior and improving the quality of care delivery, reducing practice variation, and reducing costs of health care [27-30]. Although relatively few published studies have rigorously evaluated the impact of clinical pathways on clinical outcomes and costs [29], it is widely recognized that the rigor involved in pathway development and assessment of evidence obtained is important to improving outcomes. Accordingly, many health organizations such as AHS are using clinical pathways with this intent. In support of this approach, a clinical pathway focused on the emergency management of childhood asthma has been shown to increase the use of evidenced-based therapies [29,30]. However, creation of clinical pathways (or guidelines) is not enough; active implementation strategies are needed to achieve optimal improvements in outcomes [31-34]. Two strategies that are among the most consistently successful for changing practitioner behavior and improving patient outcomes are interactive educational sessions and reminder systems [31-34].

Even if children are prescribed appropriate medications, parents frequently do not receive adequate information and education to understand the rationale and importance of using preventive medications, which often results in poor adherence [35-37]. *Adherence* refers to a patient successfully taking medication. *Primary adherence* refers to the obtaining of medication prescribed, and *secondary adherence* refers to proper completion of the regime as intended by the prescriber. A World Health Organization [38] review indicated 30% adherence to medications by children and adolescents with asthma, which is among the lowest reported for any chronic disease. There is good evidence, however, that asthma education programs for children with severe exacerbations requiring emergency department and in-hospital care sufficiently improve adherence to reduce subsequent hospitalizations, emergency department visits, and urgent disease-related physician visits by 20-30% [39].

We propose to improve the prescription and use of evidenced-based preventative therapies for children with asthma, with the goal to significantly improve their disease control and quality of life, and reduce unnecessary emergency department visits and hospitalizations by 20% each. We will achieve this by (1) installing a primary care clinical pathway for managing childhood asthma into clinicians’ electronic medical record (EMR) to facilitate the use of best evidence by practitioners, and (2) training chronic disease management (CDM) health professionals to provide targeted and timely asthma education to parents and children with asthma. We will test this pathway and education project in a representative sample of 22 Alberta primary care practices, using a pragmatic cluster-controlled trial methodology. Specifically, we will determine if our proposed innovation, as compared with usual care,...

...increases *prescription* of evidenced-based preventative therapies;...increases *dispensing* (primary adherence) of evidenced-based preventative therapies;...improves children’s *asthma control*;...improves *quality of life* for children and families; and...decreases *health care utilization* (emergent primary care visits, emergency department visits, and hospitalizations) for asthma, and decreases overall societal (health system and family) costs.

### Foundational Activities

In Spring 2011, the *AHS* Respiratory Network—now formally known as the “Respiratory Health Strategic Clinical Network (RHSCN)”*—*adopted the childhood asthma pathway initiative, in collaboration with the *AHS* child health community, as one of its 3 top priorities and provided human and financial resources to move the pathway initiative forward. The initial project of the *RHSCN* and our project team was to develop, implement, and evaluate emergency department and in-patient pathways, for which we received the *Canadian Institutes of Health Research Partnerships for Health System Improvement* funding. Concurrently, with the start of the emergency department/in-patient pilot project and the ongoing implementation of the emergency department and in-patient pathways across the province, the *RHSCN* started developing the primary care pathway.

In Fall 2013, our team developed a collaboration with the *Health Quality Council of Alberta (HQCA)* who have agreed to extract, link, and analyze health administrative data (which they routinely receive and utilize) and other data provided to them from 2 Albertan community-based primary care research networks (Northern and Southern Alberta Primary Care Research Networks—*NAPCReN* [40] and *SAPCReN*, respectively 41). These networks are regional networks contributing to the *Canadian Primary Care Sentinel Surveillance Network* (*CPCSSN*) [42]. *CPCSSN* extracts clinical data quarterly from participating practitioners’ (*sentinels*) EMRs, cleans them, removes identifiers, and makes these data available for surveillance, epidemiology, and health services research. With the principal investigator [name], *CPCSSN* is currently developing and validating a case definition and case finding algorithm for childhood asthma, which will be added in due course to its routine data extraction and processing. The networks contributing to *CPCSSN* in Alberta are currently able to process data from both the *Wolf* and *Med Access* EMR systems. These networks have agreed to assist with recruiting practices to participate in this project.

The project team has engaged extensively with frontline primary care practitioners, primary care leaders, and pediatric respirologists and allergists in developing this primary care pathway project over the last 3 years; each of these groups has heavily invested and is committed to the successful completion of our project. We have engaged frontline practitioners in the following ways: (1) being part of an interdisciplinary pathway development committee including primary care and subspecialty care practitioners with rural, regional, and urban representation; (2) conducting a small focus group (consultation) session about the content and format of the pathway with primary care practitioners at Alberta primary care conferences; (3) beta-testing of the EMR-based pathway in 4 primary care practices; and (4) surveying Alberta primary care practitioners for feedback about the pathway, its design, and practicality. The capacity to manage their asthma patients according to the best practice will be enhanced by the integration of the pathway into the EMRs and by the education given to the CDM health professionals. Participating clinics will identify an individual available for the practice who will take on the role of a CDM professional. The CDM professionals will receive a 3-hour training session/updating on asthma education with continued support from the trainer for the duration of the intervention. They will be provided with access to resources that will be available thereafter to ensure sustainability.

Currently, an asthma case definition is being developed, which is an algorithm that screens the *CPCSSN* data extracted from EMRs to accurately identify patients with asthma. Once developed, the case definition will be validated by comparing it with a gold standard established by 2 experienced physicians using 1000 pediatric *CPCSSN* records.

Network leadership will encourage their members’ participation in this initiative by introducing the study team to the medical and administrative leads of all their participating practices. Alongside *SAPCReN* and *NAPCReN* research staff, study team members will travel to eligible practice sites to inform them about the details of the project, answer any questions they might have, and then ask them to participate in this project.

### Key Stakeholders

In this project, the following 4 organizations will each play an essential role: AHS (*RHSCN)*, *HQCA*, and *NAPCReN/SAPCReN. RHSCN* and *HQCA* are committing substantial in-kind funding toward this project over the next 3 years. In addition, 3 other strategic clinical networks, namely, (1) *Maternal, Newborn, Child and Youth*, (2) *Emergency,* and (3) *Primary Care Chronic Disease Management*, share substantial common ground. A total of 3 primary care organizations, the 2 *AHS Primary and Community Care* portfolios and the *Provincial Primary Care Network*, will be “end users,” throughout the project, and will also provide critical advice as we plan our “implementation scale and spread” rollout. Participating primary care practices are also end users, providing valuable input into feasibility and sustainability. Finally, the patients of Alberta will be the final stakeholders, as we anticipate their health will be affected favorably.

## Methods

### Project Objectives

We propose a 3-year mixed-methods health services research project using a randomized cluster-controlled trial design (with primary care practices as the cluster; trial registration number NCT02481037) to achieve the following objectives:

To use the Theoretical Domains Framework (TDF) to refine our implementation strategy;To implement the intervention (a childhood asthma primary care clinical pathway in EMRs and identifying and training CDM health professionals to provide asthma education) in the 11 practices in the intervention arm;To evaluate our project intervention using interviews, health administrative and EMR databases, and child and parent surveys of quality of life, the child’s asthma control, and the socioeconomic burden of the child’s disease on their family; andTo develop a detailed “scale and spread” strategy if our intervention is shown to be successful (ie, yields either cost savings or improved child and parent quality of life) for all Alberta primary care practices who use a supported EMR.

### Intervention Development and Implementation Strategy

The development of our implementation strategy has followed the *Knowledge-to-Action Model* of Graham and colleagues [43]. This cyclic process starts with the identification of the problem—a knowledge-practice gap in the management of childhood asthma in a primary care setting—followed by synthesis of the evidence into a primary care pathway [18], assessment of potential barriers to its use, tailoring of known-effective implementation strategies to local circumstances, evaluation to determine whether the problem has improved and feedback of evaluation results to all end users (decision makers and participating practitioners).

The primary care pathway developed over 2 years by a subcommittee of the Asthma Working Group, RHSCN, was geographically representative of Alberta and included primary care practitioners (n=4), asthma educators (n=5), pharmacists (n=1), allergists and respiratory physicians (n=4), and asthma policy decision makers (n=2). This committee critically reviewed existing global and national guidelines [14,15] and recent randomized trials and systematic reviews to formulate the pathway. Drafts of the pathway were critically reviewed two times by primary care practitioners for ease of use and relevance to their practice, and revised each time.

The following sections provide a summary of the core components of the intervention to be provided to the intervention arm practices of the study:

#### Pathway Implementation Strategies

Based on previous extensive experience in implementing clinical pathways [44-46] and best evidence available [32,33,47-49], two change strategies were selected to implement the proposed project: (1) an interactive online learning module to teach primary care practitioners about the evidence for treatment strategies in the clinical pathway, and (2) user-written software installed within practitioners’ EMR that will serve as a reminder system to facilitate improved patient documentation and management. We will also use the results of a study being conducted using the TDF to identify necessary modifications to our strategy for primary care practices randomized to the intervention arm [50].

#### Development of EMR Embedded Pathway

The EMR prototype (developed in *Med Access* and currently being developed in *Wolf*) provides practitioners with dropdown menus to document key findings from medical history review and physical examination, classify patient’s disease phenotype to generate therapeutic recommendations, assess asthma control, generate a risk assessment, and print out asthma action plans and patient prescriptions.

#### Development of a Web-Based Interactive Learning Module

To ensure primary care practitioners understand the underlying rationale and evidence behind the development of the primary care pathway, practitioners randomized to the intervention arm will have easy access to a Web-based interactive learning module, which is designed to easily fit into a busy practitioner’s schedule. An equivalent module was developed by the research team and successfully used in a trial of an educational intervention in emergency room and in-patient management in Alberta [51]. Physicians and nurses will access the site with a password and will indicate completed sections before the intervention commences. A well-designed Web-based professional learning module has been shown in a previous trial to be as effective at enhancing learning and changing professional behavior as in-person interactive teaching sessions [52]. Parents will also be given access to patient-oriented Web modules to enhance the nurse-led teaching.

#### Train-the-Trainer for Patient Education

CDM health professionals working within the practices in the intervention arm will be provided 3 hours of in-person training on providing asthma education to children with asthma and their families. This training will be provided by the clinical coordinator, an experienced Certified Respiratory Educator [name].

### Project Population

Practices will be recruited from those who are currently or are becoming a member of the *NAPCReN* or *SAPCReN.* All children (1-17 years of age at the time of enrollment) who meet the case definition of asthma (and are seen by a participating primary care practitioner within a consenting practice) will be included in the trial’s analysis unless they refuse consent [53]. The *CPCSSNs* use a “social contract” consent process, where practice populations are informed generally about research, information is freely available on specific projects, and people are included unless they object [53]. Because the project will collect data outside the *CPCSSN* protocol, parents of children with asthma in the participating practices will be sent a letter by their primary practitioner outlining implied consent and asking them to complete surveys about quality of life, asthma control, and the burden (impact) of asthma on their family.

### Sample Size Calculation and Analysis

Our *AHS* partners provided the number of pediatric asthma incidences billed by each practice in the province. We will use this information to select practices that have more than 70 active, eligible asthma patients. In addition, the Primary Care Asthma Working Group of clinicians agreed the minimal clinically important difference to be 20% (see Multimedia Appendix 1 for a detailed sample size calculation).

Patients included in the analysis of the primary and one of the secondary outcomes (proportion of children dispensed a preventive medication) will be categorized as either “successful” or “not successful” based on the logic outlined in Multimedia Appendix 2. Given the clustered nature of patients’ “success” within practices, a mixed effects logistic regression model will be performed where clustering is considered. Odds ratios for success between arms will be presented along with 95% CIs. The modeling will include assessment of potential confounders and independent risk factors. To analyze the other secondary outcomes (quality of life and asthma control and emergency department visits/hospitalizations), we will use a linear mixed effects regression model, and include fixed effects for the baseline/follow-up periods, the pathway/control arms, and stratifications/interaction, and random effects to account for clustering in practices.

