### Randomization of Practices Design Issues and Potential Bias

All practices consenting to participate in this trial will be randomized, stratified for urban (Edmonton/Calgary) versus nonurban and academic (trainees routinely evaluate patients) versus nonacademic practices. A statistician not aware of our project question will allocate practices using a standard randomization software. We have chosen practices as the unit of randomization because most individual practitioners within a shared practice use the same EMR and we wish to prevent contamination. Because we are testing the effectiveness of embedding the pathway into clinicians’ EMR and train-the-trainer CDM professional education, consenting practices randomized to usual care will not have access to either intervention, and therefore the risk of significant contamination is small. In addition, the design provides an opportunity to test for contamination by comparing the difference between the pre- and post-periods for the 2 groups (ie, intervention and control).

Practices will be randomized to either:

Routine care versus interventionEmbedding a primary care clinical pathway for managing childhood asthma into clinicians’ EMR to facilitate practitioners utilizing best evidence, and training these practices’ CDM professionals to provide asthma education to children with asthma and their parents.

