### Primary Outcome

The proportion of symptomatic children with asthma in the baseline and follow-up periods (separate calculations) who are appropriately treated with a preventer will be the primary outcome. The denominator will be the number of children who meet the case definition of asthma *and* receive at least one prescription for an inhaled short-acting beta-agonist (eg, salbutamol) during the applicable period. The numerator will be, of these children, the number of those who receive a prescription for inhaled corticosteroid, montelukast, a combination of inhaled long-acting beta-agonist and corticosteroid (ie, agonist + corticosteroid), or some combination of these 3 drugs in the same period.

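### The primary logistic model names neither the baseline-period outcome nor the randomisation strata and leaves adjustment open; prespecifying both could add precision at little cost

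*Protocol article*

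**What the plan says.** All modelling statements are in the protocol article, section Sample Size Calculation and Analysis. For the primary outcome (preventer prescribed) and the dispensing outcome, "a mixed effects logistic regression model will be performed where clustering is considered". The effect measure follows: "Odds ratios for success between arms will be presented along with 95% CIs". On covariates there is one sentence: "The modeling will include assessment of potential confounders and independent risk factors".

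The remaining secondary outcomes (quality of life, asthma control, emergency visits and hospitalizations) get a linear mixed model that will "include fixed effects for the baseline/follow-up periods, the pathway/control arms, and stratifications/interaction, and random effects to account for clustering in practices".

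Two other sections show what data exist. Primary Outcome defines the endpoint as "The proportion of symptomatic children with asthma in the baseline and follow-up periods (separate calculations"), so each practice has a pre-intervention value of the same measure. The section on randomization says that practices are "stratified for urban (Edmonton/Calgary) versus nonurban and academic (trainees routinely evaluate patients) versus nonacademic practices". That section also mentions "comparing the difference between the pre- and post-periods for the 2 groups", but only as a test for contamination.

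**The concern.** The trial has a "representative sample of 22 Alberta primary care practices", 11 of them in the intervention arm. With so few clusters, stable differences in prescribing habits between practices can make up much of the error, and chance imbalance at baseline is a real possibility. A practice's own earlier prescribing rate is a natural covariate for both problems, and it is already being collected. The stratification factors are known for every practice before randomisation.

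The described primary model mentions none of these, while the next sentence attaches period and stratification terms to less important outcomes. In their place stands an open-ended confounder assessment. In a randomised trial that leaves the primary estimate dependent on choices not yet made. The text also does not tie the arm odds ratio to a period. A follow-up-only model would discard the baseline data, and pooling both periods without an arm-by-period term would dilute the effect. Finally, the agreed important difference is 20% on an outcome defined as a proportion, and a reader cannot set an odds ratio directly against it.

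**Working it through.** **The plan's own figure.** The 22 practices cannot be reproduced. Their derivation is in Multimedia Appendix 1, which is not shown, and the article gives no ICC, between-period correlation or power.

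**Inputs from the article.** 11 practices per arm. Selected practices have over 70 eligible patients. Control proportion about 50%, a proxy from the Alberta pharmacy figure in Background and Overview. Important difference 20%, not stated as absolute or relative, so both readings are used: 50% vs 60% and 50% vs 70%. Two-sided 5%, implied by the 95% interval.

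**Assumed.** m = 70 children per practice and period; ICC 0.01 to 0.10; cluster autocorrelation (CAC, the correlation of a practice's true rate between periods) 0.5 or 0.8; different children in each period.

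**Formulas** (linear approximation on the proportion scale).
- Design effect: DE = 1 + (m − 1)·ICC.
- Correlation of practice proportions between periods: r = m·ICC·CAC / DE.
- Variance ratio with baseline as a covariate: 1 − r².
- SE = √{[p₁(1 − p₁) + p₂(1 − p₂)]/(11m) × DE × (1 − r²)}.
- Power from the noncentral t with 20 df, or 19 df with the baseline covariate.

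**Worked case, ICC 0.05, CAC 0.8, 50% vs 60%.** DE = 1 + 69 × 0.05 = 4.45. r = 70 × 0.05 × 0.8 / 4.45 = 2.8/4.45 = 0.63. 1 − r² = 0.60. The unadjusted SE is √(0.49/770 × 4.45) = 0.0532, and the adjusted SE is 0.0414. Power goes from 0.43 to 0.63. A simulation of 4,000 trials per case, comparing practice-level covariance analysis with a follow-up-only t-test, gave a variance ratio of 0.62 and power of 43% and 60%, in good agreement.

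| ICC | Variance saved, CAC 0.5 | Variance saved, CAC 0.8 | Power 50% vs 60%: none / CAC 0.5 / CAC 0.8 | Power 50% vs 70%: none / CAC 0.5 / CAC 0.8 |
|---|---|---|---|---|
| 0.01 | 4% | 11% | 0.83 / 0.84 / 0.87 | 1.00 / 1.00 / 1.00 |
| 0.05 | 15% | 40% | 0.43 / 0.49 / 0.63 | 0.96 / 0.98 / 1.00 |
| 0.10 | 20% | 50% | 0.27 / 0.32 / 0.48 | 0.79 / 0.87 / 0.97 |

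**Sensitivity to cluster size.** The primary denominator is restricted to children prescribed a short-acting beta-agonist, so m may be below 70. At an assumed m = 35, ICC 0.05 and CAC 0.8, r = 1.4/2.7 = 0.52 and the saving is 27%.

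**Sensitivity to overlap.** If the same children contribute to both periods (assumed individual autocorrelation 0.5), the saving at m = 70 is 25% to 73% over ICC 0.01 to 0.10 and CAC 0.5 to 0.9.

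**Form of adjustment.** A plain difference-in-differences has variance ratio 2(1 − r), which exceeds 1 when r is below 0.5. At ICC 0.05 and CAC 0.5, r = 1.75/4.45 = 0.39 and the ratio is 1.21, so precision is lost.

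**Degrees of freedom.** Intercept, arm, baseline and two strata leave 22 − 5 = 17. In the worked case, with no gain at all credited to the strata, moving from 19 to 17 df changes power from 0.631 to 0.625.

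**The case against.** The strongest reply is that silence is not exclusion. The article never says that baseline or strata are left out, and the open confounder assessment could admit them. The remark about separate calculations describes how the proportion is computed, not how it is modelled. A journal article also commonly leaves exact covariates and degrees of freedom to an analysis plan. This stands in part: a reader might infer that the primary analysis ignores baseline and strata, and the documents support only that it does not name them. It does not remove the point, because the article does state a primary model and a way of handling covariates, and a better choice is available from data already being collected.

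Other stronger readings also fail:
- That the primary outcome gets a weaker analysis than every secondary outcome. The dispensing outcome shares the primary model. The linear model has a period effect, not a baseline-outcome covariate, and a difference-in-differences form can be less precise than follow-up alone.
- That adjusters will be chosen after seeing the data. Neither the timing nor the method of selection is given.
- That only an odds ratio will be reported. The text says that odds ratios will be presented and does not rule out other measures.
- That omitting the strata widens the interval by a known amount. This depends on how prognostic they are, which the documents do not say.

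**Conclusion.** The point holds as a worthwhile, low-cost improvement to the stated primary analysis. It is not a demonstrated error. The described model names neither the baseline-period outcome nor the strata, both are available, and the same paragraph names period and stratification terms for the other secondary outcomes.

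A reader might conclude that a large share of the trial's precision is being given up. The documents cannot support that, because ICC, CAC and the effective practice size are all assumed here. The variance saving is substantial at CAC 0.8 with ICC 0.05 or above and modest at CAC 0.5. Power is materially affected for a 10-point difference at ICC 0.05 or above. If the 20% is absolute, power is already about 0.96 at ICC 0.05 and the gain matters only at high ICC. The benefit of the strata terms cannot be sized.

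**What to change.** Prespecify the primary analysis, and the matching dispensing analysis, as follows:
- Follow-up success modelled on arm, the practice's baseline-period proportion, urban/nonurban and academic/nonacademic, with a practice random intercept.
- Baseline entered as a covariate, or through a constrained-baseline model in which both periods are modelled and the arms share one baseline mean; not a plain difference-in-differences.
- Tests and intervals based on practice-level, small-sample degrees of freedom (about 17).
- This fixed list as the primary analysis in place of the open confounder assessment; any further adjustment labelled as sensitivity analysis.
- The marginal risk difference with its 95% CI beside the odds ratio, with a statement of whether the 20% is absolute or relative.

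The cost is a change of wording before outcomes are analysed and a few practice-level degrees of freedom. No new data are needed.
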